## Introduction

 Wolfram syndrome is a rare combination of neurodegeneration and diabetes, with an estimated prevalence of 1:500 000.^1^ The minimum clinical diagnostic criteria include both diabetes mellitus and progressive optic atrophy in childhood.^2^ It shows primarily autosomal recessive inheritance, due to mutations in the gene *WFS1*.^3 4^ Approximately 50% of affected children develop signs of neurodegeneration such as cerebellar ataxia and brainstem function impairment by 15 years of age^5^; and severe vision impairment by 18 years.^6^ Up to two-thirds of affected people develop cranial diabetes insipidus, sensorineural deafness and neurogenic bladder; other complications include hypogonadism in males, neurological and psychiatric disorders.^2^ There is currently no specific treatment for this progressive disorder.

The protein*,* Wolframin, negatively regulates endoplasmic reticulum (ER) stress through suppression of ATF6 signalling,^7^ maintenance of ER calcium homeostasis,^8^ cell cycle progression^9^ and granular acidification.^10^ Depletion of Wolframin expression and/or activity results in cell death. A potent cyclin-dependent kinase inhibitor, p21^cip1^, functions as a regulator of cell cycle progression at the G1 and S phase.^11^ It inhibits the apoptosis induced by cell cycle arrest and p53 expression. We observed significant p21^cip1^ downregulation in three Wolframin-depleted cell lines at baseline; however, the expression of p21^cip1^ was associated with inhibition of progression through the G2 phase of the cell cycle and prevention of neuronal apoptosis.^12^

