### Statistical analysis

#### Sample size

The target sample size for this trial is pragmatic, driven by what is required to conduct a rigorous scientific trial and what is feasible. Using hierarchical repeated measures analyses with a 5% significance level, 80% power and accounting for an estimated 15% missing data rate, the total sample size is 70, to be recruited over all sites with no one site recruiting more than 50% of all participants. The methods of Diggle *et al* were used for the sample size calculation.^35^

A longitudinal hierarchical model analysis for VA has been chosen because: (1) Wolfram syndrome symptoms progress gradually over years; (2) a repeated measures analysis yields a feasible sample size.

We used data on a cohort of 26 patients with Wolfram syndrome, kindly provided by [name] (St Louis Wolfram Research Clinic, USA). Our calculation assumed:

Mean progression of VA loss under placebo patients was 0.082 LogMAR units per annum (p.a.).The effect of being on active treatment resulting in an effect size of 0.041 p.a. (representing a halving of the rate of progression).Homoscedastic errors distributed N (0, 0.074^2^).Random gradients N (0, $\sigma_{B}$). In the St Louis cohort data, we noted that a rapidly progressing patient inflated the estimate of $\sigma_{B}$. This patient was measured using off-chart methods, which will not be used in the primary analysis of TREATWOLFRAM. Initially, we estimated $\sigma_{B}$ to be 0.036, the estimate obtained by fitting the model to the St Louis data, excluding the patient with off-chart measurements. We assessed sensitivity to this figure (by including observations from this patient) in our simulation study.That VA LogMAR scores at baseline range from 0 to 1.6 to reflect the patients that will be recruited in the trial (VA greater than 1.6 is an exclusion criterion).

We expect that some participants will discontinue early, leading to less than 100% data collection for the primary outcome. We assume that participants provide data until they discontinue at some random point, with all subsequent observations missing. Simulations show that this method of incorporating missing data is conservative and that a target sample size of 70 participants when accounting for up to 15% data missing has a type I error sufficiently close to 5% and power approximately equal to 80%.

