#### Primary outcome analysis

The primary outcome will be analysed according to the intention-to-treat principle and longitudinal analysis of patients’ progression of VA loss between evaluations at baseline and after 36 months of treatment measured.

We expect VA loss to progress linearly in time for both placebo and VPA-treated participants, on average, although at different rates. We depart from the analysis above by proposing to analyse the series in eyes separately, corrected with glasses, nested within patient. Thus, we initially propose random intercepts for individuals and for eyes within individuals. The patient-level intercept will address the tendency for the vision in the eyes of individual patients to be highly correlated. Additionally, we expect random gradients to be necessary at the eye level to allow that each eye may have its own rate of progression.

Our proposed initial model to analyse VA is:

$$y_{ijk}=\left(\alpha +a_{i}+\;a_{ik}\right)+\left(\beta +\gamma z_{j}+b_{ik}\right)t_{j}+\;\epsilon_{ijk},\;\;i=1,\ldots ,N,\;j=0,\ldots ,6,\;k=0,1$$

Let *i* index patients, so that *i*=1, …, *N*, where *N* is the total trial sample size. Let *t*=*t_VA_* and *j* index *t*, so that *t_0_*=0 and *t_6_*=3 years, etc. Finally, let *k*=0 denote the left eye, and *k*=1 denote the right eye. Let *y_ijk_* denote VA for patient *i* at time *t_j_* in eye *k*. Let *z_i_* take the value 1 if patient *i* is allocated to VPA, else 0.

This model will be fitted in R using the packages nlme or lme4, using restricted maximum-likelihood (REML). General positive-definite covariance structure will be used.

This model assumes that: the patient random intercepts $a_{i}$ are independent for different *i*; the eye random intercepts $a_{ik}$ and slopes $b_{ik}$ are independent for different *i* and *k;* and the within-group errors $\epsilon_{ijk}$ are independent for different *i*, *j* and *k* and independent of the random effects.

Here, α is the fitted mean VA value at *t*=0, β is the mean progression in VA per annum for participants on placebo and γ is the adjustment to the mean progression in VA for participants on VPA, a term we will refer to as the treatment effect.

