### Randomisation

Eligible participants were randomly assigned on a 2:1 basis in favour of VPA to either of the two trial treatments (VPA or placebo) by the local site investigators using computer-generated randomisation at the Cancer Research UK Clinical Trials Unit (CRCTU). Trial participants were allocated a unique trial identification number via a list generated by the unblinded trial statistician using a block size of between 6 and 12. To ensure blinding was maintained, treatment allocation was not displayed; rather, pack numbers to be dispensed were shown.

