Box 1Eligibility criteria for TREATWOLFRAMInclusion criteriaPatients must meet all of the following criteria to be eligible for enrolment:A definitive diagnosis of Wolfram syndrome, as determined by the following:Documented diabetes mellitus diagnosed under 16 completed years according to the WHO or American Diabetes Association criteria and/or documented optic atrophy diagnosed under 16 completed years.ANDDocumented functionally relevant mutations on one or both alleles of the WFS1 gene based on historical test results (if available) or from a qualified laboratory at screening.Aged 6 years or older and weighing at least 20 kg.A visual acuity assessed as either the right eye or left eye having a logarithm of the minimum angle of resolution score of 1.6 or better on an Early Treatment Diabetic Retinopathy Study chart, with or without corrected vision.Written informed consent (and assent as required).Females of childbearing potential will only be included after a negative pregnancy test as per the national valproate pregnancy prevention programme or equivalent. If sexually active, they must agree to use a highly effective contraception measure and to pregnancy testing at each clinical follow-up visit.Highly effective methods include:Combined (oestrogen and progestogen containing) hormonal contraception associated with inhibition of ovulation:Oral.Intravaginal.Transdermal.Progestogen-only hormonal contraception associated with inhibition of ovulation:Oral.Injectable.Implantable.Intrauterine device.Intrauterine hormone-releasing system.Bilateral tubal occlusion.Vasectomised partner.Sexual abstinence.Sexually active men with a female partner of childbearing potential must agree to the use of condoms and the use of a highly effective method of contraception by the female partner.The patient is willing and able to meet all protocol-defined visits for the duration of the trial.Exclusion criteriaClinically significant non-Wolfram-related central nervous system involvement which is judged by the investigator to be likely to interfere with the accurate administration and interpretation of protocol assessments.A diagnosis of a mitochondrial myopathy.Active liver disease has a personal or family history of liver dysfunction related to known genetic disorders, or the patient has porphyria.Received treatment with any investigational drug within the 30 days prior to trial entry.Currently taking sodium valproate; or has a known hypersensitivity to sodium valproate or its excipients.Any other acute or chronic medical, psychiatric, social situation or laboratory result that, based on the investigator’s judgement, would jeopardise patient safety during trial participation, cause inability to comply with the protocol or affect the trial outcome.Currently breastfeeding.Known urea cycle disorders.Has one of the following disorders: lactose intolerance, the Lapp lactase deficiency or glucose-galactose malabsorption.

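### The primary model has no baseline predictor of the rate of visual loss; prespecifying age and age × time would be a nearly free gain in precision and in protection against a chance age imbalance

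*Protocol article*

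**What the plan says.** - **Model** (Primary outcome analysis). Visual acuity in each eye is regressed on time, with fixed effects α (mean at time zero), β and γ. β "is the mean progression in VA per annum for participants on placebo", and γ is the change in that slope on valproate. Random intercepts are at patient and eye level and random slopes at eye level, with a general covariance structure. The test is a t-test of γ. The model is presented as an initial proposal, with alternatives allowed if the fit is poor.
- **Entry** (Box 1). "Aged 6 years or older and weighing at least 20 kg"; no upper age is given. At least one eye must be at LogMAR 1.6 or better. The Sample size section plans for baseline values from 0 to 1.6.
- **Allocation** (Randomisation). 2:1, from "a list generated by the unblinded trial statistician using a block size of between 6 and 12". No stratification factor is named.
- **Planning figures** (Sample size). "Mean progression of VA loss under placebo patients was 0.082 LogMAR units per annum"; treatment "resulting in an effect size of 0.041 p.a"; error SD 0.074; SD of random slopes initially 0.036; and, "accounting for an estimated 15% missing data rate, the total sample size is 70".
- **Numbers recruited** (Trial status). 63 patients. The sponsor considers a 10% type I error there in order to keep 80% power.

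**The concern.** Apart from treatment, the printed model leaves all differences in rate of loss between patients to the random slopes. If some of that variation could be predicted at entry, leaving it in the random part inflates the standard error of γ, in a trial that closed seven patients short and is weighing a looser significance level.

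Age is the natural candidate. The Introduction says that about half of affected children have "severe vision impairment by 18 years", and patients whose vision is already lost cannot enter. At the planning rate, an eye passes from 0 to 1.6 in 1.6/0.082 = 19.5 years. Older people who still qualify would therefore tend to be slower progressors, while children have not been filtered in this way. With about 42 patients against 21 and no named stratification by age, one arm could be older by chance, and part of the resulting difference in slope would appear in γ.

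**Working it through.** **Inputs.** From the article: error SD 0.074, slope SD σ_B = 0.036, effect 0.041 per year, seven visits from day 0 to day 1080 (taken as 0, 0.5, …, 3 years), 2:1 allocation, 63 randomised. Assumed: an exact 42:21 split, a two-sided test, patient-level series (as in the article's own calculation), complete data, and R², the share of true slope variance explained by age. The article gives no R², so a range that includes 0 is used.

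**1. The plan's own figure.** The sum of squares of visit times about their mean is 2 × (1.5² + 1² + 0.5²) = 7.0. Variance of one patient's estimated slope = 0.074²/7 + 0.036² = 0.000782 + 0.001296 = 0.002078. At 5% and 80% power with 2:1 allocation this needs 45 evaluable patients, and 45/0.85 gives 53, not 70. A total of 70 follows if σ_B is about 0.045 (with 15% inflation) to 0.0505 (without). The article calls 0.036 its initial estimate and says that it tested sensitivity by including a rapid progressor, but prints no second value. Both 0.036 and 0.0505 are therefore carried forward.

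**2. Gain from adjustment.** Variance ratio = [0.000782 + σ_B²(1 − R²)] / [0.000782 + σ_B²]. The SE of γ is the square root of slope variance × (1/42 + 1/21). At σ_B = 0.036 and R² = 0 it is √(0.002078 × 0.0714) = 0.0122. Power = Φ(0.041/SE − 1.96).

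| R² | Variance of γ, σ_B 0.036 | Power, N = 63, σ_B 0.036 | Power, N = 63, σ_B 0.0505 |
|---|---|---|---|
| 0 | unchanged | 92.0% | 75.7% |
| 0.1 | −6% (ratio 0.938) | 93.5% | 79.0% |
| 0.2 | −12% (ratio 0.875) | 94.9% | 82.3% |
| 0.3 | −19% (ratio 0.813) | 96.2% | 85.7% |

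**3. Effect of a realised imbalance.** The SD of the difference in mean age between arms, in units of the age SD, is √(1/42 + 1/21) = 0.267. A difference of at least 0.5 SD in either direction has probability 2 × [1 − Φ(0.5/0.267)], about 6%. The shift in γ is imbalance × √R² × σ_B. At R² = 0.2 this is 0.5 × 0.447 × 0.036 = 0.008 per year, and 0.008/0.041 is about one fifth of the target. It is also about two thirds of the SE of 0.0122.

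**4. Validity of the unadjusted test.** In a simulation of per-patient slopes (40,000 runs, 42:21), its type I error over all allocations was 5.0% at R² = 0.2 and at R² = 0.5. Within the 5% of allocations most unbalanced on age it was 11.6% and 21.0%.

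**5. Cost if age is irrelevant.** At R² = 0, simulated power was 91.3% without age and 90.9% with it.

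**The case against.** The strongest reply is that nothing here is an error. An unadjusted treatment-by-time test in a randomised trial is legitimate, and step 4 shows that it holds its level. The choice of covariates is often left to the analysis plan, which is not shown, and the printed model is labelled as initial. This stands, and it is why the point is an improvement and not a defect. The fallback clause does not do the same job, however: it is triggered by poor fit and names no covariate. The Masking section says that the trial statistician is unblinded, so a term added later could look data-driven.

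Two further objections stand as limits:

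- **The link between age and rate is not documented.** The article says that loss was linear over time and gives milestones by age, but no rates by age and no age distribution. A reader might infer from the 19.5-year figure that older entrants must be slow progressors. That goes too far. Box 1 accepts diabetes and/or optic atrophy diagnosed before 16, so visual loss may start later. Only one eye need be at 1.6 or better, and 0.082 is a mean rate. The link is plausible, of unknown size, and need not be linear in age.
- **Part of a baseline-severity effect may already be absorbed.** Baseline acuity enters as an outcome with a common intercept, and the general covariance lets an eye's intercept and slope correlate. The random slopes also carry age-related variation into the SE, but they do not correct γ for an imbalance between arms.

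**Conclusion.** This is a free improvement, not an error. The printed primary model omits any baseline predictor of slope in a small trial with wide entry. If age explains 10% to 20% of slope variance, adjusting for it gains about 1.5 to 3 points of power at the printed slope SD of 0.036, or about 3 to 7 points at 0.0505. If age explains nothing, there is no gain. These figures rest on the assumed R², complete data and patient-level series; the eye-level analysis would differ somewhat.

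Three stronger conclusions are tempting and are not supported:

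- **That age imbalance biases γ.** Over all allocations γ is unbiased. The shift arises only given the imbalance that occurred, and in proportion to the age-slope relation.
- **That randomisation ignored age.** A condensed article names no stratification factor, but it does not say that there was none.
- **That 70 was wrong, or that power at 63 is 76%.** The 76% belongs to a slope SD back-solved from 70. The printed 0.036 gives about 92% with complete data.

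**What to change.** Before any unblinded outcome data are modelled, write into the primary model centred age at randomisation as a main effect and as an interaction with time:

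(α + δ·age_i + a_i + a_ik) + (β + κ·age_i + γ·z_i + b_ik)·t_j + ε_ijk

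Test γ by the same t-test and keep the printed model as a supportive analysis. If the full protocol or analysis plan already contains such a term, it is enough to state that it, and not the model printed in the article, is primary.

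The cost is one line of text and two more fixed parameters with 63 patients. Age is already known for everyone, because eligibility depends on it. If age is unrelated to slope, precision is essentially unchanged.

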### Randomisation

Eligible participants were randomly assigned on a 2:1 basis in favour of VPA to either of the two trial treatments (VPA or placebo) by the local site investigators using computer-generated randomisation at the Cancer Research UK Clinical Trials Unit (CRCTU). Trial participants were allocated a unique trial identification number via a list generated by the unblinded trial statistician using a block size of between 6 and 12. To ensure blinding was maintained, treatment allocation was not displayed; rather, pack numbers to be dispensed were shown.

### Masking

Both VPA and placebo control are distributed by a third party ensuring the receiving trial site is masked to the drug throughout the duration of the trial, that is, trial investigators and pharmacists, outcome assessors, participants and their carers are masked from the drug allocation. Only data analysts remain unblinded, that is, the trial statistician and the database programming team.

A 24-hour, 7 days a week unblinding service is provided by Emergency Scientific and Medical Services Global. The unblinding service will allow the local principal investigator, or other medically qualified person, to identify the study medication (sodium VPA or matched placebo) for an individual patient in an emergency situation.

At the end of the trial, unblinded allocations will be released to each site for feedback to the trial participants.

### AE reporting and analysis

Participants are monitored regularly for AEs (definitions are listed in online supplemental appendix 7).

The reporting period for AEs starts at the screening visit and continues until 30 days after the last IMP administration. Serious adverse events (SAEs) are reported until 30 days post end of treatment. The NCI CTCAE^19^ are used to grade each AE. The trial office records all AEs reported (nature, onset, duration, severity, outcome) evaluates them with respect to seriousness, and site-assessed causality and expectedness. Interim analysis of SAEs is performed and presented to the independent Data Management Committee (DMC) regularly.

Specific attention is given to AEs related to liver and renal function considering previous safety data relating to VPA-induced hepatic encephalopathy and interstitial nephritis. VPA is also known to have a high teratogenic potential, and children exposed in utero to VPA have a high risk for congenital malformations and neurodevelopmental disorders. We therefore monitor the outcome of pregnancies of trial participants to provide SAE data on congenital anomalies or birth defects.

### Storage of trial samples and images

Glucose is analysed at study sites. C-peptide and pro-insulin are analysed by the Core Biochemical Assay Laboratory (Cambridge, UK). VPA levels are analysed at the Regional Toxicology Laboratory, Sandwell General Hospital (UK).

MRI scans are anonymised using a Conformité Européene (CE) mark anonymisation tool at the local site, before transfer to the Clinical Trials Unit. The staff at the local centre acquiring the MRI then transfer anonymised data to a compact disc, encrypted where possible and delivered by courier to the trials office, where they are transferred to the central imaging server.

Optional consent in UK participants only is requested for:

Health records are to be flagged through the NHS Information Centre for Health and Social Care service to assist with long-term follow-up data collection.Any remaining research blood samples being stored and used for future research purposes.The collection, storage and analysis of skin samples for future research.

### Data handling, quality assurance and retention

Data management is undertaken by the CRCTU at the University of Birmingham, UK. The CRCTU is fully compliant with the Data Protection Act 1998, the International Conference on Harmonisation Good Clinical Practice (GCP) and General Data Protection Regulation (GDPR). Participant identifiable data are shared only with the clinical team on a need-to-know basis to provide clinical care and to ensure appropriate follow-up. All trial records will be archived and securely retained for at least 25 years. On-site monitoring will be carried out as required following a risk assessment and as documented in the Quality Management Plan. Further information regarding data management is provided in the study protocol.

The CRCTU will hold the final trial data set and will be responsible for sharing clinical trial data with the wider research community to maximise potential patient benefit while protecting the privacy and confidentiality of trial participants. Data anonymised in compliance with the Information Commissioners Office requirements, using a procedure based on guidelines from the Medical Research Council Methodology Hubs, will be available for sharing with researchers outside of the trials team within 12 months of the primary publication.

### Trial organisation structure

The University of Birmingham acts as the sponsor of the trial (University of Birmingham, [name]. Email: [contact]).

The Trial Management Group (TMG) is composed of the chief investigator, co-investigators representatives from each National Coordinating Centre and the trial team at the CRCTU. The TMG is responsible for the day-to-day running and management of the trial.

The TSC provides overall supervision for the trial on behalf of the sponsor and advice through its independent chair. Membership includes independent clinicians, the chief investigator, a patient/parent representative and members of the TMG as appropriate.

Data analyses are supplied in confidence to the independent DMC, operating in accordance with a trial-specific charter based on the template created by the DAMOCLES group and consisting of an independent adult physician chair, statistician and senior paediatrician.

### Trial status

Recruitment into the TREATWOLFRAM clinical trial opened in January 2019 and completed in October 2021, with 63 participants (90% of target enrolment) randomised from the six trial sites (University Hospitals Birmingham, UK 11; Birmingham Women’s and Children’s Hospital, UK 14; Almeria, Spain 18; Lodz, Poland 5; Montpellier, France 5; Paris, France 10). This number is seven fewer than planned to allow the trial to complete in a reasonable time. We calculated the minimum number of participants required to achieve 80% power while retaining an acceptable type 1 error. Accepting a type 1 error of 10%, we should still be able to achieve 80% power with 63 participants, while allowing for up to 20% attrition. Online supplemental appendix 8 summarises the recruitment rate. Treatment follow-up and data collection are ongoing, and the last trial visit will take place in November 2024. A summary of the protocol amendments is provided in online supplemental appendix 9.

